**Quality of life evaluation**

Quality of live will be evaluated by the EQ-5D questionnaire [[25](#_ENREF_25),[26](#_ENREF_26)]. EQ-5D essentially consists of two pages - the EQ-5D descriptive system and the EQ visual analogue scale (EQ VAS). The EQ-5D descriptive system comprises the following 5 dimensions: mobility, self-care, usual activities, pain/discomfort and anxiety/depression. Each dimension has 3 levels: no problems, some problems, extreme problems.

The EQ VAS records the respondent’s self-rated health on a vertical, visual analogue scale where the endpoints are labeled “Best imaginable health state” and “Worst imaginable health state” (0 is denoting the worst imaginable health state while 100 is denoting the best imaginable health state). The validity and reliability of the EQ­5D questionnaire have been tested [[27](#_ENREF_27),[28](#_ENREF_28)].

The EQ-5D questionnaire is attached in the appendix.

**Administration and regulation**

**Informed Consent**

The investigator will obtain written informed consent from the patient participating in this study after adequate explanation of the aims, methods, objectives, and potential hazards of the study and prior to undertaking any study-related procedures. The investigator must utilize a consent form for documenting written informed consent. Informed consent will be appropriately signed and dated by the patient or the subject’s legally authorized representative and the person obtaining consent.

**Confidentiality**

Subjects’ anonymity will be strictly maintained and their identities will remain protected from unauthorized parties. The information is not to be disclosed to any third party (except for medical stuff or employees or agents directly involved in the conduct of the study or as required by law).

**Study Files**

The medical records will be maintained adequately to enable good data storage and latter on management. Subjects' clinical source documents will include (but not limited to) the following: subject's hospital/clinic/ hyperbaric unit records, physician’s and nurse’s notes, appointment book, original laboratory reports, electroencephalogram (EEG), X-ray, SPECTs, CT and special assessment reports, consultant letters, screening and enrollment log, etc.

**Statistical Considerations**

## Analysis Sets

### Safety Analysis Set

The safety analysis set will consist of all subjects with whom the study treatment was initiated.

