**Objectives**

The aim of the current study is to evaluate, for the first time in a prospective cross-over, randomized study, the effect of hyperbaric oxygen therapy (HBOT) on patients with chronic neurocognitive deficiency due to mild TBI.

- The primary endpoints of the study are to evaluate the effects of the HBOT on:
- Neurocognitive function (using Mindstreams neurocognitive battery)
- Brain metabolism (as visualized by SPECT)
- The secondary endpoints included quality of life evaluation.

The safety of the HBOT in this post TBI population will also be evaluated and any adverse event will be recorded.

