***Study protocol***

After signing the informed consent, patients will be randomized in 1:1 manner into the treated or the control-cross group. After the randomization, patients will be invited for baseline evaluation that will include full review of their medical status and complete physical examination. All patients will present baseline anatomical scan (CT/MRI). After their inclusion, patients will be randomized to two groups: a treated group and a cross group. All patients will go through evaluation of their neurocognitive function using neurocognitive testing battery, quality of life using EQ-5D questionnaire and brain functional imaging (rCBF-SPECT scan). The patients in the treated group will be evaluated twice – at baseline and after 2 months of HBOT treatment. The patients of the cross group will be evaluated three times – at baseline, after a 2 month control period of no treatment and after a consequent 2 month period of HBOT treatment. We emphasize that the study will be a cross-over trial and patients in the cross group will receive HBOT treatment after their second evaluation and will go through a third neurological evaluation after the cross, when they will complete their HBOT.

The following HBOT treatment protocol will be practiced: The patients will go through 40 HBO treatments (each treatment session will be given on a separate day), distributed over two months (five days a week). Each session will be for 60 minutes in 100% oxygen atmosphere and at pressure of 1.5 ATA.

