## Statistical Analysis

### Safety Analysis

Adverse events will be tabulated by treatment group, severity and relation to treatment.

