**Adverse Events**

An adverse event (AE) is any untoward medical occurrence in a clinical investigation subject administered a medicinal product and which does not necessarily have a causal relationship with this treatment. An AE can therefore be any unfavorable and unintended sign, symptom, or disease temporally associated with the use of a medicinal product, whether or not considered related to the medicinal product. Pre-existing events, which increase in severity or change in nature during or as a consequence of use of a medicinal product in human clinical trials, will also be considered AEs.

Any medical condition or clinically significant laboratory abnormality with an onset date before the screening visit and not related to study procedures is considered to be pre-existing, and should be documented in the case report form.

Any AE (i.e., a new event or an exacerbation of a pre-existing condition) with an onset date after the screening visit up to the last day on study (including the follow-up, off study medication period of the study), should be recorded as an AE on the appropriate CRF page(s).

An AE does not include:

- Medical or surgical procedures (e.g. surgery, Endoscopy, tooth extraction, transfusion); the condition that leads to the procedure are an adverse event.
- Pre-existing diseases or conditions or laboratory abnormalities present or detected prior to the screening visit that does not worsen.
- Situations where an untoward medical occurrence has not occurred (e.g. hospitalization for elective surgery, social and/or convenience admissions).
- Overdose of either study drug or concomitant medication without any signs or symptoms unless the subject is hospitalized for observation.

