***Serious Adverse Events***

**A** **serious adverse event** (SAE) is defined as follows:

Any adverse drug experience occurring at any dose that results in any of the following outcomes:

- Death;
- Life-threatening situation (subject is at **immediate** risk of death);
- In-patient hospitalization or prolongation of existing hospitalization (excluding those for study therapy or placement of an indwelling catheter, unless associated with other serious events);
- Persistent or significant disability/incapacity;
- Congenital anomaly/birth defect in the offspring of a subject who received study drug;

Other: medically significant events that may not result in death, be immediately life-threatening, or require hospitalization, may be considered a SAE when, based upon appropriate medical judgment, they may jeopardize the Subject and may require medical or surgical intervention to prevent one of the outcomes listed in this definition.

Examples of such events are:

- Intensive treatment in an emergency room
- Blood dyscrasias or convulsions that do not result in hospitalization
- Development of drug dependency or drug abuse

The investigator should notify the Institutional Review Board (IRB) or Independent Ethics Committee (IEC) as soon as is practical, of serious events in writing where this is required by local regulatory authorities, and in accordance with the local institutional policy.

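### The safety set admits only patients who started HBOT, so cross-group patients who leave during the untreated two months are lost from the adverse-event table, and the AE and SAE definitions do not fit that period

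*Protocol*

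**What the plan says.** **Who is analysed.** Protocol, Safety Analysis Set: "The safety analysis set will consist of all subjects with whom the study treatment was initiated". The condition concerns the patient; no period is named.

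**When treatment starts.** Protocol, Study protocol: the cross group is evaluated "at baseline, after a 2 month control period of no treatment and after a consequent 2 month period of HBOT treatment". The treated group goes from its baseline evaluation to HBOT with no such waiting period.

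**How events are shown.** Protocol, Safety Analysis: "Adverse events will be tabulated by treatment group, severity and relation to treatment".

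**What counts as an event.** Protocol, Adverse Events, defines an AE as "any untoward medical occurrence in a clinical investigation subject administered a medicinal product". Protocol, Serious Adverse Events, opens its definition with "Any adverse drug experience occurring at any dose that results in any of the following outcomes".

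**What is to be recorded.** The Adverse Events section also requires recording of any AE "with an onset date after the screening visit up to the last day on study", and a parenthesis extends this to off-medication follow-up. The Objectives add: "The safety of the HBOT in this post TBI population will also be evaluated and any adverse event will be recorded".

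**The concern.** There are two linked problems.

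1. **Set membership depends on something that happens after randomisation, and it happens later in one arm.** A treated-group patient enters the safety set at the first session, soon after baseline. A cross patient enters only after staying in the study for two untreated months. Those who deteriorate or lose interest in that time are the ones who may never enter. Yet the untreated period is the only concurrent source of background event rates. The Background section lists headaches, seizures and sleep disorders among the consequences of TBI, so background events are to be expected. If the patients lost are disproportionately those with events, the untreated rate is too low and HBOT compares unfavourably for a reason unrelated to HBOT.

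2. **The definitions are worded for patients who have received a product.** They were not adapted to a design in which half the patients are untreated for two months. They sit badly with the recording rule in the same part of the protocol, so two sites or two data reviewers could treat the same control-period event differently.

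**Working it through.** The protocol states no figure on this point, so there is none to reproduce. The check traces patients through the rules and then illustrates the size.

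**Step 1. Three patient types**

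| Patient | In the safety set? | Control-period events |
|---|---|---|
| Treated group, starts HBOT | Yes | None (no control period) |
| Cross group, completes the control period and starts HBOT | Yes | Inside the recording window; nothing in Safety Analysis Set or Safety Analysis removes them |
| Cross group, leaves before HBOT | No | Absent from the safety analysis, even if on the case report form |

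The loss is confined to the third row.

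**Step 2. Definitions against the recording rule**

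- The AE definition requires a patient who has been given a product. The SAE definition requires a drug experience at some dose. Neither wording naturally describes an event before any HBOT.
- The recording rule runs from after screening to the last study day, which includes the control period. The Objectives promise that any adverse event is recorded.
- The rule applies to AEs, a term already defined through product administration. Its off-medication wording refers to follow-up, which more naturally means time after treatment than time before it.

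Both readings can be defended from the text, so the text is inconsistent.

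**Step 3. How many patients could be lost**

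Assumption: a proportion *d* of cross patients leaves during the control period. The protocol gives no value; 5% to 30% is used as a range. Allocation is 1:1 (Randomization). Sample Size Considerations gives N = 31 without saying whether this is the total or per group, so both are shown.

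Patients lost = (cross-group size) × *d*; share of all randomised = *d*/2.

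| *d* | 31 in total (15.5 cross) | 31 per group | Share of randomised |
|---|---|---|---|
| 5% | 0.775 | 1.55 | 2.5% |
| 10% | 1.55 | 3.1 | 5% |
| 20% | 3.1 | 6.2 | 10% |
| 30% | 4.65 | 9.3 | 15% |

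**Step 4. Effect on the control-period event rate**

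Let *n* be the number of cross patients and *x* the number with a control-period event. Let *a* and *b* be the numbers with and without an event who leave before HBOT. The rate seen in the safety set is (*x* − *a*)/(*n* − *a* − *b*). Assumed: *n* = 30 and *x* = 6, a true rate of 6/30 = 20%.

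- Half of those with an event leave and nobody else does (*a* = 3, *b* = 0): 3/27 = 11.1%.
- Half leave regardless of events (*a* = 3, *b* = 12): 3/15 = 20%, no bias.
- Only patients without an event leave (*a* = 0, *b* = 3): 6/27 = 22.2%, a small bias the other way.

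Both the direction and the size depend on whether leaving is linked to having an event. These rates concern the control period alone. A cross-group column not split by period would also contain HBOT-period events.

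**The case against.** **A treated-only safety set is common and matches the stated aim**, which is the safety of HBOT; no comparative safety hypothesis is stated. This stands for describing HBOT itself, and the fix keeps such a summary. It does not answer the problem for a table by treatment group, where the cross column is the natural reference and its membership is filtered by two months of retention.

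**Period-specific tables are often left to an analysis plan**, which may exist here. That is fair as to layout. But the protocol itself fixes the set, and a period split within that set would still omit cross patients who were never treated.

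**A reader might infer that all control-period events drop out of the safety data, so that the background rate would read as 0%.** The documents do not support this. The set restricts patients and not periods, the recording window covers the control period, and the Objectives promise that any event is recorded. Even the literal definition does not clearly give zero: every patient has a baseline SPECT scan with an injected radiopharmaceutical, which could itself be read as a medicinal product.

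**A reader might also infer that serious events before HBOT, including those from SPECT, would go unreported.** This is not shown either. Assessment of Adverse Events asks for the relationship to study procedures as well as to the study drug, and the ethics-committee notification sentence speaks of serious events without repeating the drug condition. The SAE wording is loose; a failure to report does not follow from it.

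**The illustration is a chosen case.** This stands. The 11.1% figure has event-related departure only, and no figure in the protocol supports or excludes it.

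**Conclusion.** The point holds in a limited form. Cross patients who leave before their first HBOT session are excluded from the safety analysis by a condition that arises after randomisation and applies about two months later in one arm. The control-period reference is biased downwards if patients with events are more likely to leave, and it is unbiased if leaving is unrelated to events. Under assumed control-period dropout of 5% to 30%, the exclusion removes 2.5% to 15% of all randomised patients. In the illustrative case a 20% background rate appears as 11.1%. These sizes rest wholly on assumed rates.

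Separately, the AE and SAE definitions are inconsistent with the recording window and with an untreated period, and must be reconciled. The primary efficacy analysis is not affected. The wording should still be corrected, because the safety of HBOT is a stated aim and the untreated period is its only concurrent comparison.

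**What to change.** 1. **Safety Analysis Set.** Define two summaries. (a) Control-period safety in all randomised cross patients, from the start of the recording window to first HBOT or withdrawal, whichever comes first. (b) HBOT-period safety in all patients of either group with at least one session.
2. **Adverse Events and Serious Adverse Events.** Reconcile the definitions with the recording rule, so that both terms cover any enrolled participant whether or not HBOT has been given.
3. **Reporting.** Give the number of cross patients who left before HBOT and their events. State, wherever the two periods are compared, that ascertainment differs: patients on HBOT are seen five days a week, whereas the control period has scheduled evaluations only at its start and end. Using the same form in both periods will not remove that difference.

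Cost: wording changes in three sections and one extra table, with no additional patients or visits. The remaining limitation is the unequal ascertainment in item 3, which the change discloses but does not cure.

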### Primary Efficacy Analysis Set

The primary endpoint parameter: *improvement in neurocognitive tests scores* will be measured following HBOT treatment for post TBI patients suffering from chronic neurocognitive deficiencies.

The primary efficacy analysis evaluation will include all subjects who completed the HBOT treatment or the control period, had no major protocol violations, and for whom there is a valid *mindstreams score* at baseline and following 2 months of HBOT treatment.

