**Exclusion criteria**

Patients will be excluded if they will have one of the following criteria:

- Dynamic neurologic improvement or worsening during the past month;
- Had been treated with HBOT for any other reason prior to their inclusion;
- Have any other indication for HBOT;
- Chest pathology incompatible with pressure changes;
- Inner ear disease;
- Patients suffering from claustrophobia;
- Inability to sign written informed consent;
- Smoking patients will not be allowed to smoke during the study and if they would not comply with this demand they will be excluded.

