**Randomization**

Since the diversity of the patients included in the study, after signing the informed consent is expected to be high, no stratifies criteria will be used. Patients will be randomized in 1:1 fashion to either treatment or controlled-cross group.

There will be no placebo in the cross group during the control period. The only way to give “placebo” of HBOT, is to bring the patients to the hyperbaric chamber and to increase the environmental pressure in a way the patients will “feel the hyperbaric pressure” in their ears. However, Henry’s law states: “the amount of a given gas dissolved in a given type and volume of liquid is directly proportional to the pressure of that gas in equilibrium with that liquid”. Thus, hyperbaric environment significantly increases the dissolved oxygen pressure even if a person holding his breath [[29](#_ENREF_29)]. Moreover, the alternative of hosting the patients in the hyperbaric chamber without any pressure increase cannot serve as a real placebo since the patients will not feel the pressure. Accordingly, the only real “placebo” could be achieved by increasing the pressure and reducing the percentages of the oxygen but that holds significant safety consideration.

From the ethical point of view, it is deemed unethical to “treat” the patients (40 sessions in the hyperbaric chamber) while they actually know that it is a placebo. In order to somewhat compensate for this limitation, the control will be a cross group and after the 2^nd^ evaluation at the end of a control period they will be crossed to HBOT. The cross for treatment enables intra-group efficacy evaluation in both treatment and control group.

Since the patients will know they are not receiving HBOT during the control period they will not be blinded with regard to the treatment arm. Accordingly, the quality of life evaluations will not be blinded. However, the complete blindness evaluation can be assured in both of the primary end points of this study, The Mindstreams computerized evaluation and the brain SPECT evaluation done by the radiologist.

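### The primary efficacy set admits only compliant completers with a post-HBOT score, contradicts itself for the cross group, and no all-randomised efficacy set is stated

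*Protocol*

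**What the plan says.** The Protocol defines two analysis sets. The safety set holds subjects in whom study treatment was started. The primary efficacy set is defined thus: "The primary efficacy analysis evaluation will include all subjects who completed the HBOT treatment or the control period, had no major protocol violations". Subjects must also have a valid Mindstreams score "at baseline and following 2 months of HBOT treatment". The conditions are joined by *and*. No third set is stated.

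Allocation is 1:1: "Patients will be randomized in 1:1 fashion to either treatment or controlled-cross group". Under Study protocol, the cross group is assessed "at baseline, after a 2 month control period of no treatment and after a consequent 2 month period of HBOT treatment". The treated group is assessed at baseline and after 2 months of HBOT. On the treatment course, the same section says: "The patients will go through 40 HBO treatments", on separate days, five days a week. On timing it says: "After the randomization, patients will be invited for baseline evaluation". The Randomization section says that patients will know their arm.

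Under Exclusion criteria, smokers may not smoke during the study, and "if they would not comply with this demand they will be excluded".

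Primary Efficacy Analysis sets H0: p1 = p2 against p1 > p2. It then declares success if the one-sided lower 95% limit of one success proportion, in a cohort that it does not define, is at or above 0.12.

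**The concern.** Completion, absence of major violations and a valid post-HBOT score are all known only after randomisation. Even the baseline score may be, given the order in Study protocol. A set built on such conditions need not keep the balance that randomisation gave. Patients know their arm, and the treated arm must attend 40 sessions while the control arm need only return for testing. Whether a patient stays can therefore depend on how the patient is doing.

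The score condition adds an asymmetry. A treated patient qualifies at month 2, but on a literal reading a cross-group patient qualifies only at month 4. Events after the control period has ended can then decide who counts in a comparison at month 2.

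The Protocol itself fixes this set as primary, so this is not a detail left to an unseen SAP. Scores that are never collected from early stoppers cannot be recovered at the analysis stage.

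**Working it through.** **1. Plan figures.** The Protocol gives no dropout or violation rate and no retention figure to reproduce. Its one related number is N = 31. A one-sample, one-sided normal approximation for 12% versus 2% gives [(1.645·√(0.02·0.98) + 0.842·√(0.12·0.88)) / 0.10]² = 25.4, so 26 and not 31. That mismatch is a separate matter and does not affect this point. All loss rates below are assumptions.

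**2. Who qualifies, by the text.**

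| Patient | Completion clause | Score clause, read literally |
|---|---|---|
| Treated, finishes HBOT, tested at month 2 | met | met at month 2 |
| Treated, stops early | not met | does not matter |
| Cross, finishes control and later HBOT, tested at month 4 | met | met at month 4 |
| Cross, tested at months 0 and 2, does not complete later HBOT | met through the control period | not met |

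In the last row the two clauses of one sentence give opposite answers.

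**3. Retention on the literal reading.** Assume loss d in each 2-month period. The treated arm keeps 1 − d and the cross group keeps (1 − d)².

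| d | Treated | Cross |
|---|---|---|
| 5% | 95% | 90% |
| 10% | 90% | 81% |
| 20% | 80% | 64% |
| 30% | 70% | 49% |

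If the control period alone is enough, this extra loss disappears, but the set is still compliant completers only.

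**4. Effect on the single-cohort proportion.** If a share d is excluded and every excluded patient is a non-success, the observed proportion is p/(1 − d). For p = 0.12:

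- d = 5%: 0.12/0.95 = 12.6%
- d = 10%: 0.12/0.90 = 13.3%
- d = 20%: 0.12/0.80 = 15.0%
- d = 30%: 0.12/0.70 = 17.1%

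This is the upper bound for each d. If exclusion is unrelated to success, the proportion stays at 12%. If successes are lost more often, it falls below 12%.

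**5. Effect on the decision rule.** Assume that 31 is the number analysed. The lower limit is p − 1.645·√(p(1 − p)/n), with the exact limit in brackets.

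- 7/31 = 22.6%: limit 0.102 (0.111), fails.
- 8/31 = 25.8%: limit 0.129 (0.135), passes.
- The same 8 successes among 35 entered (31/0.90 = 34.4, rounded up), 8/35 = 22.9%: limit 0.112 (0.119), fails.
- The same 8 among 39 entered (31/0.80 = 38.75, rounded up), 8/39 = 20.5%: limit 0.099 (0.106), fails.

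Under this worst-case assumption, the choice of set alone can change a result near the threshold.

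**The case against.** The strongest reply is that the success rule does not use a between-arm contrast. It compares one cohort's lower limit with 0.12, the sample-size text measures improvement against the patient's own baseline, and the Randomization section presents the crossing as allowing evaluation within each group. For a within-patient proportion, a baseline and a post-HBOT score are coherent requirements. This stands for that analysis, and the fix keeps the condition there. It does not clear the set: the stated hypotheses compare p1 with p2, and selecting completers can distort a single-cohort proportion as well.

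A second reply is that mention of the control period shows that completing it was meant to suffice. That may be so, but the score clause says otherwise and the two must be reconciled. Under the milder reading the set is still compliant completers.

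Three stronger readings are tempting, and the documents support none of them.

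- *The result is biased towards HBOT.* The two sources of loss point to different arms: 40 sessions burden the treated arm, while the literal score clause removes more of the cross group. No dropout data are given, so direction cannot be derived.
- *The bias can be stated in score points against a 10-point target.* The Protocol states percentages and a success proportion. It gives no such point target and no SD of change.
- *Smokers' data are deleted.* The Exclusion criteria say that non-compliant smokers are excluded, but not whether from treatment, follow-up or analysis.

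**Conclusion.** The concern holds in this form. The Protocol makes a compliant-completer set primary and states no all-randomised efficacy set, and its score clause conflicts with its completion clause for cross-group patients. These are facts of the text and need no assumption.

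The consequence is a risk of bias in both the comparison of p1 with p2 and the single-cohort proportion. Its size and direction are not derivable from the documents. The illustrative figures (12% appearing as 13.3% at 10% loss or 15.0% at 20%) rest on an assumed loss rate and on every excluded patient being a non-success. The retention gap of 9 points (90% versus 81%) or 16 points (80% versus 64%) rests on the literal reading and on equal loss in each period.

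**What to change.** - Define the primary efficacy set as all randomised patients in their assigned arm, using baseline and month-2 scores regardless of sessions completed or later HBOT.
- Invite patients who stop early to the month-2 test that is already planned.
- Obtain the baseline score before randomisation. Study protocol now places the baseline evaluation after it, and mentions randomisation a second time after inclusion, so the order should be stated once.
- Keep the present set as a per-protocol sensitivity analysis. Require the post-HBOT score only for the within-patient post-HBOT analysis, which removes the conflict over the control period.
- State that the smoking exclusion does not remove data already collected from the analysis.

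The cost is amendment wording and the effort of bringing early stoppers back to a visit already scheduled. Some month-2 scores will still be missing and need a prespecified method. The estimate may be somewhat smaller than in completers.
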